### Study population

A total of 40 transtibial amputees aged between 18 and 65 years will be recruited for this study. Participants will be recruited from a major regional prosthetics center and from the greater north Florida community via relationships with local prosthetic clinics and amputee support groups. Study flyers, social media posts, and online web advertisements will also be used. Participants will be eligible if they meet the following inclusion and exclusion criteria. Inclusion criteria: men or women aged 18–60 years, traumatic transtibial amputation more than 1 year prior to enrollment, current prosthesis worn for at least 6 months, suffering from chronic LBP (>3 months with at least three pain episodes per week), must have regular access to a computer for Skype®, or a mobile phone or iPAD to perform Facetime; prosthesis K-level of K2 or greater (indicating the subject is able to ambulate and traverse low-level environmental barriers such as curbs, stairs, or uneven surfaces) [20]. Exclusion criteria: dysvascular amputation, acute back injury, pregnancy, any other chronic back pathology (i.e., herniated disc, ankylosing spondylosis, other related neurological disease), pain symptoms or functional limitations (including those that may require assistive devices) that preclude participation in resistance exercise or physical activity, back surgery within the past 2 years that restricts daily physical activities, and currently enrolled in any other resistance or strengthening exercise interventions. Written informed consent will be obtained from each participant.

The primary outcome of the study is the Numerical Pain Rating Scale (NRS_pain_) value for LBP. Sample size estimation indicated that a total sample size of 32 was necessary to detect clinically meaningful differences in NRS_pain_ from baseline to week 12. Based on published evidence of comparative studies of resistance exercise and controls on LBP [21], a sample size of 16 per group will yield a power of 80% at an *α* value of 0.05. To account for the anticipated dropout rate of 25%, the enrollment target will be 40.

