### Pain severity and pain impact on QOL

The primary outcome will be the change in the 11-point NRS_pain_ score during rest and activity from baseline to 3 months. The scale has anchors of 0 (no pain) to 10 (worst imaginable pain). The NRS_pain_ is an accepted outcome measure as described in the Initiative on Methods, Measurement, and Pain Assessment in Clinical Trials (IMMPACT) [38]. Participants will rate their current, worst, and best NRS_pain_ scores over the last 24 h, and the scores will be averaged to create the resting NRS_pain_ value [39]. The participants will also be asked to rate their pain severity during walking [40]. The number, type, scheduled nature of the medication and the medicine dose used to self-manage LBP symptoms will be self-reported by participants at baseline and weeks 4, 8, and 12.

One general QOL instrument and two disease-specific instruments will be used to determine the impact of LBP on participant perceptions of QOL [37]. General QOL will be measured by the Medical Outcomes Short Form-36 (SF-36), consisting of eight domain scores and two component scores (Mental, Physical). The SF-36 instrument has been used to track QOL after traumatic injury such as amputation [41]. Higher scores reflect higher QOL. Low back pain-specific QOL will be measured using the modified version of the Oswestry Disability Index (ODI) [42] and the Roland Morris Disability Questionnaire (RMDQ) [43]. The ODI contains 10 questions about the patient-perceived impact of pain on personal care, walking, lifting, sitting, standing, sleeping, sex life, social life, and traveling. The RMDQ consists of 24 items relating to difficulties with daily activities, house work, stair climb, walking, speed of movements, standing, appetite, and sleep. Both instruments are valid, reliable, reproducible, and sensitive to treatment interventions [42, 43]. Higher scores for both instruments reflect greater pain impact and disability due to pain.

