### Statistical analysis

Statistical analysis will be performed using the Statistical package for the Social Sciences (SPSS v. 24, IBM Corporation, Armonk, NY, USA). An *α* level will be established at 0.05 a priori for all statistical tests. Data will first be examined for normal distribution using the Kolmogorov-Smirnov test, and skewness and kurtosis parameters. Descriptive statistics will be performed to characterize the participants. Means, standard deviation, and frequencies will be obtained for both study groups. The chi-square test for frequency distributions will be used for demographics, and amputation type. Continuous data that are not normally distributed will be transformed prior to analysis.

The main analysis type that will be used to test the hypotheses of aims 1 and 2 will be a mixed-model, repeated measures approach. These analyses will examine the main effects of the exercise treatment on the study outcomes. The independent variables will include study group (HBRX or CON) and time point (baseline, week 12). Dependent variables will include LBP severity, medication use, perceived impact of LBP on QOL (NRS_pain_, medication number, SF-36, ODI, RMDQ) and biomechanical measures (walking velocity, temporal spatial parameters, GRF, key joint angles). Mixed models are the preferred approach to analyze data with repeated measures; these models account for correlation among repeated measurements, flexible time effects, and handle missing data. To test the hypothesis of aim 3, regression analyses will be used to identify significant contributors to the change in pain over 12 weeks. A hierarchical approach will be used to find the model of best fit. Independent variables that will be entered into the models will include changes in lumbar muscle strength, ultrasound measure of lumbar extensor cross-sectional area, and change scores in SF-36, ODI, and RMDQ. In addition to age, sex, and K-classification, models will be adjusted for other participant characteristics if differences are found from baseline to week 12 (Tampa Scale of Kinesiophobia and Pain Catastrophizing Scale scores, daily step number). Subjects who dropped out or missing participant data will not be included in the final analysis, and intention-to-treat will not be utilized. Due to the relatively small study size, actual treatment effects that would be seen may be washed out during an intention-to-treat analysis.

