Strengths of the study include a single-assessor-blinded, randomized controlled design. The main study outcomes will be assessed at baseline and at week 12. The outcomes include a combination of objective and subjective measures to capture the exercise adaptations and the patient experience. Objective measures include biomechanical gait parameters, muscle morphology, muscle strength, and daily step count. Subjective, patient-reported outcomes will include pain and its impact on overall QOL. The instruments and tests that will be administered are well-accepted, valid, reliable and sensitive to change [38, 42, 43]. Exercise benefits will be offered to all enrolled participants; the CON group will wait the 12 weeks before beginning the training.

In summary, the findings from this study will help to determine whether a HBRX program for unilateral transtibial amputees with chronic LBP can decrease pain severity and positively impact several physiological and mechanical factors that contribute to LBP. After adjusting for participant characteristics, our analyses will determine the relative contribution of these exercise-induced changes in these factors on pain responsiveness in this population. Future trials can be designed to target the factors we identify here as effective in reducing LBP.

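### Aim 3 searches for a best-fitting model with 8 to about 11 terms on about 30 participants at an uncorrected 0.05, which cannot support naming factors effective against back pain

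*Protocol article*

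**What the plan says.** The Statistical analysis section of the protocol article tests aim 3 by regression, to pick out the significant contributors to 12-week pain change. It states: "A hierarchical approach will be used to find the model of best fit". The significance "level will be established at 0.05 a priori for all statistical tests"; no correction for several predictors is given.

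The variables listed there are:
- changes in lumbar strength, lumbar extensor cross-sectional area, SF-36, ODI and RMDQ;
- age, sex and K-classification as adjusters;
- kinesiophobia (TSK), catastrophizing (PCS) and daily steps, if they differ between baseline and week 12.

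Other sections are less conditional. Daily step count makes step change an aim 3 covariate outright. Participant characteristics treats TSK and PCS as necessary to the aim 3 model, and adds any other variable that changes during the study. The SF-36 is described as "consisting of eight domain scores and two component scores (Mental, Physical", that is, ten scores, and the article does not say which one enters.

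On numbers, Study population says: "To account for the anticipated dropout rate of 25%, the enrollment target will be 40". On the analysis set, Statistical analysis says: "Subjects who dropped out or missing participant data will not be included in the final analysis". Compliance and attrition also removes non-compliers.

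The Discussion concludes: "Future trials can be designed to target the factors we identify here as effective in reducing LBP".

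**The concern.** With three to four participants per coefficient, a regression fits a good deal of noise. If the model is then chosen for fit and its terms are read one by one at 0.05, the chance of naming at least one factor that has no relation to pain change is well above 5%. The p-values and variance explained also look better than they are.

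Aim 3 is one of three stated hypotheses, and the Discussion proposes to build later interventions and trials on the factors it names. A false lead here would be carried forward. The primary comparison of pain between groups is not affected.

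**Working it through.** **The plan's own figures.** The only sample-size statement concerns the primary pain outcome: "Sample size estimation indicated that a total sample size of 32 was necessary". No difference or SD is given, so 16 per group cannot be reproduced from the document. The enrolment target of 40 matches 32 × 1.25 = 40. Dividing by the retained fraction would give 32 / 0.75 = 42.7, that is, 43. With 40 enrolled and 25% lost, 40 × 0.75 = 30 remain. No sample size or power is stated for aim 3.

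**Number of coefficients.** Five change scores (SF-36 as one score) plus age, sex and K-classification gives 5 + 3 = 8. Adding TSK, PCS and step change gives 8 + 3 = 11. More than one SF-36 score, or K-classification entered as several indicators, would add to this.

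**Expected R-squared when nothing predicts.** With p terms and n participants, R-squared follows a Beta(p/2, (n − p − 1)/2) distribution, with mean p/(n − 1). At n = 30:
- 8 terms: 8/29 = 0.28
- 11 terms: 11/29 = 0.38

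The chance that R-squared exceeds 0.25 is 0.55 with 8 terms and 0.85 with 11.

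**False contributors in the full model, no search.** For five independent tests, 1 − 0.95^5 = 0.23. The tests share one error variance on few degrees of freedom, so simulation is the better guide (20,000 runs, all predictors null, two-sided 0.05, correlation among the five hypothesised predictors of 0, 0.3 or 0.6). The n = 24 rows assume further losses to non-compliance or missing data; the n = 32 rows use the stated required sample.

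| Analysed n | Terms | Participants per term | Expected R-squared | At least one of the five significant |
|---|---|---|---|---|
| 24 | 8 | 3.0 | 0.35 | 19–20% |
| 24 | 11 | 2.2 | 0.48 | 18–19% |
| 30 | 8 | 3.75 | 0.28 | 20–21% |
| 30 | 11 | 2.7 | 0.38 | 19–20% |
| 32 | 8 | 4.0 | 0.26 | 20–21% |
| 32 | 11 | 2.9 | 0.35 | 20% |

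**With a search.** The article does not define the search, so these figures rest on assumed rules at n = 30.
- Forward entry at 0.05 after age, sex and K-classification, five candidates: a false contributor in about 15% (correlation 0.7) to 24% (uncorrelated) of null trials. More candidates raise this.
- Backward elimination with removal at p > 0.10: one of the five hypothesised predictors is retained and significant in about 30–32% (8 terms) or 37% (11 terms).

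**With a gate.** If individual terms were read only after a significant overall F test, the rate of naming any false contributor would return to about 5%. A block F test on the change in R-squared also holds about 5%. Neither is stated.

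**The case against.** The strongest reply is that hierarchical regression ordinarily means blocks entered in an order set by the investigators, tested by the change in R-squared, and that such a test holds about 5%. Adjusted R-squared also averages zero under the null: for 8 terms at n = 30, 1 − (21/29) × (29/21) = 0. A separate analysis plan might settle both. Part of this stands: the stepwise figures depend on an assumed algorithm and are not the rate of the plan as written. But the point rests on what the article does state: a long predictor list, best fit as the goal, adjusters chosen partly by observed change, and contributors named at 0.05. The full-model rate of about 20% needs no search at all.

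A reader might infer more than the documents support:
- **Up to 20 coefficients, or a 50% false-contributor rate.** Twenty terms need all ten SF-36 scores in one model, which the article does not say. A rate near 50% needs 14 uncorrelated candidates and forward entry. Across correlations from 0.7 to 0 the range is about 25–51%, and ten scores from one questionnaire are unlikely to be uncorrelated.
- **An analysis of the exercise arm alone, with about 15 participants.** Hypothesis 3 refers to changes induced by the exercise programme, but the analysis section does not restrict aim 3 to that arm.
- **Results that are mostly chance and will not replicate.** The figures assume that nothing predicts pain change. That is implausible for ODI and RMDQ, which measure the impact of pain. Even under a complete null, about four in five full-model analyses would flag none of the five.
- **A misleading R-squared that will be published.** The article never says that R-squared will be reported, adjusted or not.

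**Conclusion.** The concern holds at 8 to about 11 terms on about 30 complete cases. With no true predictor, expected unadjusted R-squared is 0.28 to 0.38, and a false contributor appears among the five hypothesised predictors in about 20% of trials, four times the nominal 5%. These figures assume 25% dropout, one SF-36 score, two-sided tests and coefficients read singly without a gate. They change little for n between 24 and 32, except that expected R-squared rises as n falls.

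The defect is in the stated rule and in the strength of the Discussion's claim. Aim 3 as written can suggest candidate factors; it cannot establish that they are effective. The matter should be corrected, but it leaves the primary analysis untouched.

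**What to change.** Replace the best-fit search with one pre-specified aim 3 model:
- **Tested predictors:** the three in hypothesis 3 (end of the Background section), namely change in lumbar-extension 1-RM, change in one named lumbar cross-sectional area, and change in one named quality-of-life score.
- **Covariates:** a short fixed set, not chosen by observed change, and reconciled with the Daily step count and Participant characteristics sections. The second describes TSK and PCS as baseline measures, while the analysis section conditions on their change to week 12. Remove the open-ended clause on other changing variables.
- **Error control:** a Holm correction across the three tests, which keeps the chance of any false contributor at or below 5%, against 1 − 0.95^3 = 0.14 uncorrected.
- **Reporting:** coefficients with 95% confidence intervals, and adjusted or optimism-corrected R-squared. Report the remaining candidates descriptively.
- **Wording:** call aim 3 hypothesis-generating in the Discussion, both where it says the findings will guide later interventions and in the closing sentence on future trials.

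The three predictors alone have a null expected R-squared of 3/29 = 0.10. With, for example, three covariates it is 6/29 = 0.21, so the correction to R-squared is still needed.

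The cost is wording only, with no new data. Fewer factors are formally tested, and the reported variance explained will be smaller.

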Determining the contribution of exercise-induced changes in mechanical factors, such as gait asymmetries and loading to LBP responsiveness, will be important for optimizing treatments for amputees. Over half of lower limb amputees suffer from chronic LBP [9], but there are not yet protocols in place to help these patients self-manage this pain. Our statistical procedures will help identify the greatest contributors to changes in NRS_pain_ scores from baseline to week 12. Our findings will guide subsequent interventions to maximize the factors that can have the greatest impact on pain severity for this population. There is a chance that anticipated benefits will not be detected in all study outcomes at the conclusion of the study. There is the possibility that pain does not decrease, but function, gait, and QOL improve. An interpretation could be that gait and compensatory motions after amputation are not primary causes of LBP. The improvement of gait symmetry and mechanical loading are still significant benefits for overall functional QOL. Reduction of movement asymmetries can potentially decrease the risk of other secondary musculoskeletal conditions such as osteoarthritis of the lower extremity joints. There is also the possibility that pain decreases over time, but gait symmetry does not. These findings would indicate that: (1) atrophy-related muscle weakness following amputation facilitates the onset of back pain, and strengthening these muscles is an important therapeutic goal and (2) asymmetrical movement may not be the primary cause of LBP development in amputees. According to prior work, the expected decrease in back pain from resistance exercise will be beneficial for subsequent reduction of back pain-related disability [20], reduction of pain catastrophizing [20], improvement in QOL [21] and increase in steps per day [54]. An opportunity then arises for further research to identify what different types and intensity of exercises may improve gait in lower extremity amputees.

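### Aim 3 uses changes in SF-36, ODI and RMDQ as predictors of pain change over the same 12 weeks, although the protocol describes them as consequences of pain, so it cannot support claims about what reduces low back pain

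*Protocol article*

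**What the plan says.** The Statistical analysis section of the protocol article says that "regression analyses will be used to identify significant contributors to the change in pain over 12 weeks", using a hierarchical search for the best-fitting model. The listed predictors begin with the muscle measures: "Independent variables that will be entered into the models will include changes in lumbar muscle strength, ultrasound measure of lumbar extensor cross-sectional area". Three questionnaires complete the list, which ends "and change scores in SF-36, ODI, and RMDQ". On covariates the section adds: "In addition to age, sex, and K-classification, models will be adjusted for other participant characteristics if differences are found from baseline to week 12". The characteristics it names for this are kinesiophobia, catastrophizing and step count. The sections on daily step count and participant characteristics are firmer. They name step change as an aim 3 covariate without any condition, and call kinesiophobia and catastrophizing necessary to the model.

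Hypothesis 3, at the end of the Background, has changes in lumbar strength, lumbar cross-sectional area and perceived quality of life predicting the pain response.

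Three other places bear on direction:

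- The Statistical analysis section lists SF-36, ODI and RMDQ among the dependent variables for aims 1 and 2.
- The section on pain severity and pain impact says that higher ODI and RMDQ scores mean more pain impact and more disability resulting from pain.
- The Discussion says "the expected decrease in back pain from resistance exercise will be beneficial for subsequent reduction of back pain-related disability", and in the same sentence expects better quality of life and more daily steps to follow.

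The Discussion closes: "Future trials can be designed to target the factors we identify here as effective in reducing LBP".

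**The concern.** A regression meant to find what drives pain change should not condition on variables that pain change itself moves. The protocol's own account puts ODI and RMDQ, and by its Discussion quality of life too, downstream of pain. All are measured over the same baseline-to-week-12 interval, so timing cannot separate cause from effect. Once such scores are in the model they absorb variation in the outcome. The coefficients for strength and cross-sectional area then no longer answer the mechanistic question, and the questionnaires look like leading contributors because they partly restate the outcome.

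Aim 3 is one of three stated aims, and its result is offered as a list of targets for later trials. A ranking headed by disability questionnaires, with a real strength effect hidden beneath it, would send that work in the wrong direction.

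**Working it through.** **Plan's own figure.** The article gives no sample size or power for aim 3. Its 32 evaluable participants (16 per group) are for the pain comparison only. Forty enrolled with 25% dropout leaves 40 × 0.75 = 30 completers. The 85% compliance rule can lower this further.

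**Terms.** Two muscle change scores + three questionnaire change scores + age, sex and K-classification = 8. Kinesiophobia, catastrophizing and steps bring this to 11. SF-36 has eight domain and two component scores, so 8 is a floor for the candidate list.

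**Direction.** Hypothesis 3 and the aim 3 model run from quality of life and disability to pain. The outcome description (ODI, RMDQ) and the Discussion (disability, quality of life) run from pain to those scores. The article does not reconcile the two.

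**Size of the bias.** The following inputs are assumptions, not document figures. All variables are standardized, the true strength effect on pain change is β = 0.50, and each of three questionnaire changes is a pure consequence of pain change with correlation r. The expected strength coefficient once all three are entered is

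β × A / (A + 3B), with A = 1/(1 − β²) = 1/0.75 = 1.333 and B = r²/(1 − r²).

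| r | 3B | A/(A + 3B) | strength coefficient |
|---|---|---|---|
| 0.5 | 1.000 | 0.571 | 0.29 |
| 0.6 | 1.688 | 0.441 | 0.22 |
| 0.7 | 2.882 | 0.316 | 0.16 |

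Sample size does not appear in the formula, so recruiting more participants would not reduce the bias.

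**Consequences at n = 30.** This is a simulation with 3,000 runs per setting. Strength and cross-sectional-area changes are assumed to correlate 0.5, cross-sectional area has no effect of its own, the adjusters are pure noise, and tests are two-sided at 0.05.

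| r | terms | power for strength without the three scores | with them | at least one questionnaire significant |
|---|---|---|---|---|
| 0.5 | 8 | 66% | 36% | 84% |
| 0.5 | 11 | 60% | 32% | 76% |
| 0.6 | 8 | 65% | 29% | 93% |
| 0.6 | 11 | 59% | 26% | 89% |
| 0.7 | 8 | 65% | 22% | 98% |
| 0.7 | 11 | 60% | 19% | 95% |

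The terms column counts the full model; the comparison model has three fewer. A rerun with a different seed agreed within simulation error. If the two muscle measures are taken as uncorrelated, power starts higher, at about 76%, and falls to between roughly 25% and 45%. The pattern is the same.

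**Secondary: model size.** With no true association the expected unadjusted R² is p/(n − 1): 8/29 = 0.28 and 11/29 = 0.38. A best-fit search adds optimism to that.

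**The case against.** The strongest defence is that hypothesis 3 says predict, and prediction does not need causal order. If aim 3 claimed only association, entering the questionnaires would be a weak choice rather than an error. But the article goes further: it seeks contributors to pain change and offers factors effective in reducing back pain.

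A reader might infer several stronger points. The document does not support them.

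- *The model has too many terms to identify anything.* At n = 30 a large single effect (partial f² = 0.35, assumed) still has about 87% power with 8 or 11 terms. A medium one (f² = 0.15) has 53% or 52%. Size brings weak, unstable estimates, not impossibility. Hierarchical entry may also mean that the terms never all share one final model.
- *The null R² of 0.28 to 0.38 measures the harm.* It does not. Adjusted R² removes that inflation, the article does not say that raw R² will be reported, and the figure says nothing about consequences used as predictors.
- *Leaving out study group and baseline pain is an error.* The article lists what the models will include, not a complete specification, and does not say whether the arms are pooled. A group term matters only if they are, and hypothesis 3's focus on changes induced by the exercise programme also fits an analysis of that arm alone.

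It is also fair to say that removing the questionnaires changes part of a stated hypothesis, so the hypothesis must be amended openly.

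**Conclusion.** The concern holds in this form: aim 3 enters as predictors three scores that the protocol elsewhere treats as aim 1 outcomes and as consequences of pain, so the closing claim about factors effective in reducing back pain is not supported. Under the stated assumptions, a true strength effect of 0.50 would appear as 0.29 to 0.16, and a pure consequence would be named a contributor in most trials. The exact sizes depend on the assumed effect and correlations. The direction of the bias depends only on the questionnaires being downstream of pain, which is the protocol's own description. If causation in truth ran both ways, the shrinkage would differ, but the same-interval model still could not separate the two.

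The ratio of terms to participants and the best-fit search make matters worse but are secondary. A reader might infer that the primary result is compromised. It is not, because aim 3 does not touch the randomised comparison of pain. The change should be made, but the trial's main conclusion does not hang on it.

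**What to change.** 1. Make the main aim 3 analysis one prespecified model of pain change on change in lumbar strength and change in lumbar cross-sectional area. Leave SF-36, ODI and RMDQ change out. Keep the adjusters to a short prespecified set, include baseline pain score, and add study group if both arms are pooled. State whether they are.
2. Report the quality-of-life and disability change scores separately, as correlates of pain change.
3. Amend hypothesis 3 in the Background to match.
4. In the Statistical analysis and Discussion sections, replace the language of contributors and effectiveness with association with change in low back pain, and label aim 3 exploratory.

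The cost is that the quality-of-life part of hypothesis 3 becomes descriptive and the claim for future trials is softer. No new data or visits are needed.
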